# Non-inferiority of a hybrid outpatient rehabilitation: a randomized controlled trial (HIRE, DRKS00028770)

**DOI:** 10.1186/s44247-023-00013-4

**Published:** 2023-04-25

**Keywords:** Hybrid rehabilitation, Telemedicine, Telehealth, Back pain, Randomized controlled trial, Non-inferiority study

## Abstract

**Background:**

Physiotherapeutic telerehabilitation in various musculoskeletal and internal diseases, including back pain, might be comparable to face-to-face rehabilitation or better than non-rehabilitation. In Germany, a standardized back school for patients with chronic back pain is provided in outpatient rehabilitation centers. The effectiveness of this standardized back school was shown in a randomized controlled trial in face-to-face rehabilitation. This study examines non-inferiority of a hybrid rehabilitation applying a digital version of the standardized back school against a rehabilitation applying the face-to-face back school.

**Methods/design:**

We recruit 320 patients in eight German outpatient rehabilitation centers. Patients are randomized equally to the intervention and control groups. Patients aged 18 to 65 years with back pain are included. Patients lacking a suitable private electronic device and German language skills are excluded. Both groups receive the standardized back school as part of the 3-week rehabilitation program. The control group receives the back school conventionally in face-to-face meetings within the outpatient rehabilitation center. The intervention group receives the back school online using a private electronic device. Besides the back school, the patients participate in rehabilitation programs according to the German rehabilitation guideline for patients with chronic back pain. Hence, the term “hybrid” rehabilitation for the intervention group is used. The back school consists of seven modules. We assess data at four time points: start of rehabilitation, end of rehabilitation, 3 months after the end of rehabilitation and, 12 months after the end of rehabilitation. The primary outcome is pain self-efficacy. Secondary outcomes are, amongst others, motivational self-efficacy, cognitive and behavioral pain management, and disorder and treatment knowledge. Guided interviews with patients, physicians, physiotherapists and other health experts supplement our study with qualitative data.

**Discussion/aim:**

Our randomized controlled trial aims to demonstrate non-inferiority of the online back school, compared to conventional implementation of the back school.

**Trial registration:**

German Clinical Trials Register (DRKS00028770, April 05, 2022).

**Supplementary Information:**

The online version contains supplementary material available at 10.1186/s44247-023-00013-4.

## Background

Over the last decade, the usage of technology in rehabilitation has grown exponentially, paving the way for the development of telerehabilitation and the opportunity for more flexible implementation of rehabilitation [1]. The benefits of telerehabilitation were mainly linked to better continuity of treatment when patients returned to their home environment from rehabilitation centers [2]. Especially in aftercare, telerehabilitation can help to consolidate achieved outcomes [3, 4]. In secondary prevention, telerehabilitation is beneficial to integrate therapeutic measures into the everyday life of the patient [3]. Moreover, the World Federation of Occupational Therapists has issued a statement on the use of telemedicine to improve accessibility to occupational therapy and other benefits, such as an effective support for the transition to home life [5]. Not least due to the SARS-CoV-2 pandemic, telerehabilitation was often the only form of rehabilitative care and tested worldwide [6–8]. Particularly, regions with a low supply density of rehabilitation services could profit from these interventions [8]. Since approximately 80% of those aged 14-years and older in Germany use the internet regularly, the required skills for participation in internet-based interventions are a given among the patients [9].

A survey from 2019/2020 showed that 61.3% of German adults suffered from back pain during the last 12 months. Low back pain occurred more often than neck pain in a ratio of two-to-one. Women were affected more often by low back pain (60%) and neck pain (54.9%) than men (56.4% and 36.2%). Around 15.6% of German adults develop chronic back pain (women 18.5% and men 12.4%) [10]. Due to sick leave, usage of health care services, and disability pensions, back pain is associated with high costs [11, 12].

Physical exercise can reduce pain and improve mobility, which is why it plays an important role in today’s pain rehabilitation programs [13]. However, reduced chronic low back pain observed in physical therapy does not appear to be sustained over the long term, providing an opportunity for telerehabilitation services to ensure continuity and sustainability [14].

Although a systematic review of exercise-based telemedicine in patients with chronic pain found no difference in physical activity, activities of daily living, and quality of life [15], telerehabilitation interventions have been shown to be beneficial in achieving improvements in low back pain to maintain or reduce the dropout rate through so-called “booster sessions” conducted via a mobile app [14] and video conferences [16]. In the study by Crane and colleagues, patients with chronic pain favored intermediate telerehabilitation programs that included feedback and monitoring technologies, as well as direct face-to-face counseling and exercises [17].

Whilst considerations on the implementation of telerehabilitation in Germany have so far been largely limited to rehabilitation access [18, 19] and rehabilitation aftercare [4], a current overview of systematic reviews suggests that physiotherapeutic telerehabilitation in diseases such as arthrosis, low back pain, hip and knee replacements, multiple sclerosis, and also within the framework of cardiac and pulmonary rehabilitation, can achieve as comparable or better outcomes as personal rehabilitation or non-rehabilitation [20]. Nonetheless, the included studies in the systematic reviews ranged from the years 2002 to 2016, whereas technologies have improved in the meantime [21, 22]. Newer technologies such as smartphone apps were not investigated [21] or stated to be understudied [22]. Additional differences between the studies, for example the definition and duration of back pain or delivery of the intervention, make an interpretation of the study’s findings difficult.

The study we are planning compares a hybrid rehabilitation program that implements an online back school with conventional face-to-face back school. The back school curriculum developed by the Federal German Pension Insurance [23] is the standard back school in all participating outpatient rehabilitation centers. Effectiveness of this back school was shown in a randomized control trial within standard face-to-face inpatient rehabilitation [24].

## Objectives

We hypothesize that patients receiving the hybrid rehabilitation program achieve as comparable pain self-efficacy as patients receiving the back school within a conventional rehabilitation program. Additional comparable outcomes are expected for other variables. Guided interviews explore the structure and processes of the hybrid rehabilitation program.

### Trial design

Our study is a randomized controlled trial. We recruit participants in eight outpatient rehabilitation centers. Each center provides 40 patients. In total, we recruit 320 patients. Within each rehabilitation center, participants are randomized equally to the intervention and control group. Randomization schedules were stratified for each rehabilitation center and used block randomization. Four measurement points are planned (start of rehabilitation, end of rehabilitation, 3 months after end of rehabilitation, 12 months after end of rehabilitation). We examine the non-inferiority of the hybrid rehabilitation program. Primary outcome is pain self-efficacy at the 12-month follow-up [25]. We also assess and analyze qualitative data using guided interviews with 20 patients and 18 experts. The interviews are carried out by phone.

## Methods

### Study setting

Eight centers for outpatient rehabilitation are involved in recruitment, data collection, and implementation of the rehabilitation program. All centers are located in seven different German cities (Berlin, Bielefeld, Frankfurt am Main, Jena, München, Paderborn, Regensburg). The intervention and control groups are recruited in the same rehabilitation center, but the online back school of the intervention group is used at the patients’ homes and is provided by a web-based rehabilitation provider (Caspar Health).

### Eligibility criteria

Rehabilitants aged 18 to 65 years and with back pain (ICD-10 M50 to M54, post-acute and acute rehabilitation) are included. Patients without stable internet, an appropriate electronic device for using the internet or executing app-related videos, and a suitable camera for communication are excluded. We also exclude patients not speaking German.

### Treatment

#### Intervention* group*

The intervention group receives a hybrid rehabilitation program, during which a standardized back school is delivered digitally. The standardized back school developed from the Federal German Pension Insurance consists of seven modules and is based on the health action process approach and the fear-avoidance beliefs model [24, 26]. The back school teaches knowledge about the development and maintenance of back pain, communicates a positive functional image of the back, demonstrates and practices exercises to strengthen the back, reflects how pain is mentally processed, and promotes the transfer of physical activity in everyday life. The Caspar application is used for the digital implementation of the back school. Table 1 shows a detailed overview of the back school in the intervention group, based on the Template for Intervention Description and Replication (TIDieR) checklist [27] and the TIDieR-Telehealth checklist [28].

**Table 1 Tab1:** Description of the intervention group based on the TIDieR checklist and the TIDieR-Telehealth checklist

**Brief name**	Digital back school (hybrid rehabilitation)
**Why**	The back school aims to increase physical activity in everyday life, according to the health action process approach, and to change cognitive patterns towards pain that lead to pain chronicity, based on the fear-avoidance beliefs model [26]
**What (materials)**	All content of the back school is digitalized and accessible online, via app or web browser, using the Caspar application. Patients use their private electronic device to participate. A study assistant within each outpatient rehabilitation center gives oral and practical instructions on correct use of the Caspar application and hands out a booklet with further information on the program, including the individual login account of the patient. The multimedia content contains educative videos and videos on physical exercises. For interactive meetings, the electronic device must be equipped with a suitable camera. Furthermore, patients can communicate with a health care professional (HCP), in particular physiotherapists, individually through a chat box at any time during the week
**What (procedures)**	The back school consists of seven modules [23]: (1) fundamentals; (2) back health and physical activity; (3) body awareness and spine stabilization; (4) mental factors; (5) posture and movement sequences in everyday life and at work; (6) physical activity in everyday life Part 1; and (7) physical activity in everyday life Part 2
**Who provided**	Caspar Health is a private company that provides all features of the Caspar application. The Tele-Therapie Klinik Berlin is a telemedicine clinic and provides all HCPs that guide the interactive sessions in the intervention group online, including the chat. These HCPs are experienced and specialized in digital therapy. The Tele-Therapie Klinik Berlin plans, organizes, and schedules all the interactive meetings
**How**	The entire rehabilitation program is implemented online, using the Caspar application. Group interactive meetings are performed by an HCP via camera. Non-interactive parts of the modules are performed by each patient independently
**Where**	The patients participate in the intervention from home. The HCPs operate from the buildings of Tele-Therapie Klinik Berlin or from home
**When and how much**	The seven modules are completed within 3 weeks. Each module requires 45 min to complete. The patients can choose freely when to use the educational videos and the videos on physical exercises during the week. In addition, every week a 45-min live interactive meeting is conducted online via camera and a video conference tool. Interactive meetings are scheduled during the afternoon. The participants can choose from different time slots. In addition to the online back school, patients follow their individual 3-week rehabilitation program in the outpatient rehabilitation centers. Treatments in the rehabilitation programs follow the therapy standards developed by the Federal German Pension Insurance for the rehabilitation of chronic back pain [29]
**Tailoring**	No specific tailoring of the intervention to the patient is planned. Nevertheless, during the weekly interactive meeting and in the chat, patients can receive individual feedback from the physiotherapist and apply it accordingly (e.g., change a physical exercise if painful)
**Modifications**	Not applicable
**How well**	No strategies are implemented to maintain adherence to rehabilitation. However, it is registered if and how often the patients watched the videos and if patients joined the weekly interactive meetings. Therapy adherence is measured and assessed by the researchers at the University of Lübeck

#### Control group

The control group receives a conventional rehabilitation program, during which the standardized back school is provided in face-to-face meetings. Table 2 shows a detailed overview of the back school in the control group, based on the Template for Intervention Description and Replication (TIDieR) checklist [27] and the TIDieR-Telehealth checklist [28].

**Table 2 Tab2:** Description of the control group based on the TIDieR checklist and the TIDieR-Telehealth checklist

**Brief name**	Face-to-face back school (conventional rehabilitation)
**Why**	The back school aims to increase physical activity in everyday life, according to the health action process approach, and to change cognitive patterns towards pain which lead to pain chronicity, based on the fear-avoidance beliefs model [26]
**What (materials)**	Several materials are used during the back school, such as a patient information booklet, LCD projector, and presentation sheets. A detailed list of required materials can be found elsewhere [23]
**What (procedures)**	The back school consists of seven modules [23]: (1) fundamentals; (2) back health and physical activity; (3) body awareness and spine stabilization; (4) mental factors; (5) posture and movement sequences in everyday life and at work; (6) physical activity in everyday life Part 1; and (7) physical activity in everyday life Part 2
**Who provided**	All outpatient rehabilitation centers are members of the Nanz Medico GmbH & Co. KG group. Each outpatient rehabilitation center provides their own experts from various fields (e.g., physicians, physiotherapists, or psychologists) to implement the back school
**How**	All interventions are carried out in groups within the outpatient rehabilitation centers via face-to-face meetings. Outside of the meetings, patients can make use of their materials, such as the patient information booklet, in order to practice or do the exercises
**Where**	All meetings take place in the outpatient rehabilitation center
**When and how much**	The seven modules are completed within 3 weeks. Each module requires 60 min to complete. In addition to the back school, the patients follow their individual 3-week rehabilitation program in the outpatient rehabilitation center. The treatments in the rehabilitation programs are in accordance with the therapy standards developed by the Federal German Pension Insurance for the rehabilitation of chronic back pain [29]
**Tailoring**	No specific tailoring of the intervention to the patients is planned. Nevertheless, during the meetings patients can receive individual feedback from the performing medical expert and apply it accordingly (e.g., change a physical exercise if painful)
**Modifications**	As all included outpatient rehabilitation centers are separate institutions, slight variations in performing the standardized back school may occur
**How well**	No strategies are implemented to maintain adherence to rehabilitation. However, it will be registered if patients joined each module or not. Therapy adherence will be measured and assessed by the researchers of the University of Lübeck

### Ancillary and post-trial care

No harm due to study participation is expected. Therefore, no ancillary and post-trial care are intended.

### Outcomes

All outcomes, including measurement points and expected scaling, are shown in Table 3. Since no adverse events are expected, no plans for collecting, assessing, reporting, or managing of adverse events were made.

**Table 3 Tab3:** Measures, assessment, expected scaling, and measurement occasions

Outcome	Source and reference	Scaling	Scoring	Measurement time points			
				**Start of rehabilitation**	**End of rehabilitation**	**3 months follow-up**	**12 months follow-up**

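### No adverse events are recorded in either arm, so a non-inferiority result on pain self-efficacy could not be accompanied by any comparative statement on harm

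*Protocol article*

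**What the plan says.** The protocol article decides the matter under Outcomes: "Since no adverse events are expected, no plans for collecting, assessing, reporting, or managing of adverse events were made". The section on ancillary and post-trial care rests on the same premise: "No harm due to study participation is expected. Therefore, no ancillary and post-trial care are intended". Data monitoring provides neither an outside committee nor criteria for ending the study early. Table 3 lists no adverse event outcome.

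Table 1 describes the online arm. "The patients participate in the intervention from home". "The multimedia content contains educative videos and videos on physical exercises". "Non-interactive parts of the modules are performed by each patient independently". Live contact is limited but present: "every week a 45-min live interactive meeting is conducted online via camera and a video conference tool", and a chat with a health care professional is available. The rest of the 3-week programme takes place in the centre. Under Tailoring, the example of individual feedback is "change a physical exercise if painful". Table 2 gives the same example for the control arm, whose back school is held in face-to-face groups in the centre.

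Statistical analysis plans a non-inferiority test on pain self-efficacy with a margin of -4 points. It adds superiority tests of the secondary outcomes, meant to help state a preference between the two treatments if non-inferiority is shown.

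**The concern.** The reason given for recording nothing is that nothing is expected. An expectation is not evidence, and under this plan it can never be checked, because absence of events could not be told from absence of recording. The protocol's own descriptions treat a painful exercise as something that may arise in either arm. The setting and supervision of part of the exercise also change between arms, and this is where a reader would want to see counts side by side.

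What is at stake is the reach of the conclusion. A non-inferiority result on pain self-efficacy will be read by people deciding whether to deliver the back school online, and the protocol itself intends to go on to a preference between the two modes. A preference formed without any harm data is incomplete. A few exacerbations in one arm could leave the mean pain self-efficacy score almost unchanged.

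**Working it through.** The plan gives no figure on harm, so there is none to reproduce. The check has two parts.

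**1. Could another planned source supply harm counts by arm?**

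- Table 3 measures pain, functional capacity, current health status and current sickness absence in both arms at all four time points, and weeks of sickness absence at three. These are scores and absence data, analysed as adjusted group differences. They carry no event count, severity, relation to back-school exercise or reason for stopping.
- From the discharge reports, the protocol derives treatments and their duration (Other outcomes).
- The two-weekly video conference (Auditing) covers recruitment, response rates and current matters. It is not systematic recording by arm.
- The guided interviews cover 20 patients and 18 experts. They are qualitative and cannot give a rate.
- A participant who withdraws consent has all data deleted, so an exacerbation that led to withdrawal would leave no trace.

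None of these gives a harm count.

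**2. What would recording give?**

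Inputs: 160 per arm (Sample size, planned recruitment) and 121 per arm (half of the stated minimum of 242). The second is used only as a lower scenario for the number of respondents. All event rates below are assumptions, since the protocol gives none.

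*Upper bound if no event is reported among n respondents* (one-sided 95%): 1 - 0.05^(1/n).

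- n = 160: 1 - 0.05^(1/160) = 0.0185, about 1.9% (rule of three: 3/160 = 1.9%).
- n = 121: 1 - 0.05^(1/121) = 0.0245, about 2.4%.
- The upper limits of two-sided 95% intervals, 1 - 0.025^(1/n), are 2.3% and 3.0%.

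*Chance of at least one event in an arm of 160*: 1 - (1 - p)^160.

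- p = 0.5%: 55%
- p = 1%: 80%
- p = 2%: 96%
- p = 5%: above 99.9%

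*Power to detect a difference, 160 per arm, two-sided 5%*: Φ((|p2 - p1| - 1.96·SE0)/SE1), with SE0 from the pooled rate and SE1 from the separate rates.

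- 1% vs 3%: SE0 = √(2·0.02·0.98/160) = 0.01565; SE1 = √((0.0099 + 0.0291)/160) = 0.01561; Φ((0.02 - 0.03068)/0.01561) = Φ(-0.68) = 25%.
- 2% vs 5%: 31%
- 5% vs 10%: 40%
- 5% vs 15%: 85%

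Recording would therefore bound the rates and show a large difference, but not a small one. Without recording, none of these quantities can be stated.

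**The case against.** Several stronger readings are tempting, and the protocol does not support them.

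- *The protocol contradicts itself on painful exercise.* The example illustrates individual feedback and appears for both arms. Adapting a painful exercise in a patient with back pain is not necessarily an adverse event. The wording shows that such events are foreseeable; it does not contradict the Outcomes sentence or suggest that the online arm carries more risk.
- *The online arm exercises unsupervised.* Only the non-interactive parts are done alone. There is a weekly live meeting, a chat and the in-centre programme, and control patients may also practise outside their meetings. Supervision is not the only contrast either: provider and module length (45 versus 60 minutes) also differ.
- *Eligibility points to higher risk.* The criteria admit "post-acute and acute rehabilitation", but the protocol gives no risk information for these patients.
- *Nothing would show harm.* A clear group-level worsening could appear in pain, function, health status or sickness absence.
- *The trial claims safety it cannot support.* No safety conclusion is announced. The aim is non-inferiority on pain self-efficacy.

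It can also be said that the remedy is weak. The bounds above need zero events and the stated number of respondents. An item that includes marked worsening of back pain will probably not return zero, postal follow-up brings non-response, and power is low for small differences. That is fair, and it limits what the item can deliver.

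What remains is that the protocol states outright that no plan exists, so this is not detail left to a fuller document, and none of the points above supplies a harm count.

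**Conclusion.** The point holds as a limit on what the trial can conclude. As written, the study can report non-inferiority on pain self-efficacy and indirect group differences in pain, function, health status and sickness absence. It cannot report any rate, bound or comparison of harm, although it intends to state a preference between the two deliveries.

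The size of the gain from recording is modest. It is an upper bound of about 1.9% per arm if none of 160 respondents reports an event, or 2.4% with 121, and reasonable power only for large differences (85% for an assumed 5% versus 15%, 25% for 1% versus 3%). These figures rest on assumed rates and on the stated numbers of respondents. A reader should not infer that the online back school is less safe, or that the protocol claims it is safe. The documents support neither.

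**What to change.** 1. Replace the adverse event sentence under Outcomes with a statement of what is recorded, how and when.
2. Add one closed item, identical in both arms, to the end-of-rehabilitation and follow-up questionnaires not yet issued: injury or marked worsening of back pain related to back-school exercises (no / yes / yes with medical contact or stopping the exercises).
3. Report it descriptively by arm and questionnaire, with 95% CI and the number of respondents as denominator. No hypothesis test is needed.
4. Limit the conclusion to pain self-efficacy and state that small differences in harm cannot be excluded. If the item cannot be added, the report should say that comparative safety was not assessed.

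The cost is one questionnaire item and an ethics notification. Recruitment was still running at publication, and the follow-up questionnaires are mailed centrally, so the change is practicable. The downside is partial coverage, because patients already past these questionnaires will lack the item, and self-report in an unblinded trial is coarse. How events are to be managed clinically is for the sponsor and investigators to settle and is not proposed here.
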